#### Cost-effectiveness

For the cost-effectiveness evaluation, patients will complete the EQ-5D-5 L, the most commonly used health-related QoL instrument [70], and the ICEpop CAPability measure for Older people (ICECAP-O), a 5-item well-being scale [71], and caregivers will fill out the CarerQol-7D. In addition, the Institute for Medical Technology Assessment Valuation of Informal Care Questionnaire (iMTA iVICQ) [72] will be used to assesses the amount, costs, and appraisal of the care provided by the caregivers. The iMTA Medical Consumption Questionnaire (iMTA MCQ) consists of 31 questions regarding healthcare utilization [73] and incorporates direct healthcare use of the patient. Both the iMTA MCQ and the iMTA iVICQ will be sent to the caregivers and can be completed at home.

#### Qualitative endpoint data

A random selection of one out of four of the dyads in the intervention group will be invited to participate in the qualitative part of this study, accounting for the site and disease stage. Semi-structured interviews will be conducted in order to achieve more insight into the experiences of participants who underwent the DICE method and what they considered as helpful elements. The interviews will be conducted face-to-face, will be audio-taped, and will last approximately 60 min. Interviews will be performed until saturation is reached, i.e., until no new concepts and themes are obtained [84], which we estimate to reach after we interviewed 15–20 patients with their caregivers [8, 85, 86]. Questions will be asked in an open non-directive manner, focusing on the subjects’ thoughts, feelings, and experiences. Topics include the subjects’ experience of the intervention, and which elements were considered to be effective and which not, with the aim to examine the efficacy of and experiences with the DICE method from the perspective of patients and caregivers.

### Sample size

In order to reach sufficient power to detect reliable and clinically relevant changes, we performed a power calculation using *G*Power*. The power calculation is based on the results of a recent meta-analysis by Kim and Park [17], on the effectiveness of PCC in a mix of institutionalized and community-dwelling patients, and the results of a pilot study on the effectiveness of the DICE method in community-dwelling patients and caregivers [36]. Both studies showed a moderate effect size for the effects of PCC interventions on QoL in patients with AD and their caregivers when compared to CAU. Since there are limited validated sample size calculation methods for the mixed model approach we aim to use [87], our calculation is based on a repeated measures ANOVA. Using *G*Power*, the required sample sizes were *N* = 86 and *N* = 46 for between- and within-group analyses, respectively, based on a power of 0.80 and an alpha of 0.05. After enquiry, the 6 recruitment centers suggested that at least 25 patients receive a MCI or AD diagnosis annually at each site. Though there are a high number of patients available at all 6 study sites, the participation of eligible dyads is expected to be 150 since not all patients will fulfill our criteria or will be willing to participate (based on an estimated inclusion rate of 40% [88]). We will carefully keep track of the reasons why eligible subjects refuse to participate. We will recruit a total of 150 patients during the total inclusion period of approximately 3 years (*N* = 75 in the control group and *N* = 75 in the intervention group), which exceeds the estimated needed sample size, even when accounting for dropout/loss to follow-up.

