#### Primary outcomes

The QoL of the patient will be measured by the Quality of Life in Alzheimer’s Disease (QoL-AD) questionnaire [67]. This is one of the most widely used QoL questionnaires in AD and has good psychometric properties [80]. Patients are questioned via a 13-item interview format. The proxy version of the QoL-AD is also used and filled out by the caregiver since previous studies have shown that the caregivers’ perspective on the patients’ QoL might be a more valid indicator of treatment success [81].

The CarerQol-7D will be used to measure the care-related QoL in caregivers [53]. The instrument includes six burden dimensions and a subjective valuation scale for happiness.

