### Statistical methods

*T*-tests or chi-square tests will be used to identify the differences in baseline characteristics (e.g., age, education level, disease severity) between the control group and the intervention group. For the primary and secondary study outcomes, we will use an intention-to-treat approach including all subjects irrespective of the adherence to our intervention [89]. Thereafter, we will perform per-protocol analyses with only the subjects who completed the intervention (underwent all DICE steps). We will correct for multiple testing.

We will use the Little’s Missing Completely at Random Test to examine whether the data are missing at random or missing completely at random. The mixed model analyses will be able to handle the data when the missing data is completely at random. Multiple imputation will be used in cases when data is missing at random.

Linear mixed models will be used for the primary and secondary outcomes for the T0, T1, and T2 time points. These statistics are preferred when using longitudinal data because of its advantage in handling missing data and its capacity to deal with nested data and variance in follow-up duration between and within the groups. Changes in the trajectories of the primary and secondary outcomes are compared between the two groups. Subject, hospital, and time are considered as random effects, and baseline measure, group, and disease severity are accounted as fixed effects.

We will perform a cost-utility analysis of the intervention group versus the control group in accordance with the Dutch guidelines for economic evaluations on the basis of questionnaires [90].

Quality and length of life will be combined into quality-adjusted life years (QALYs) using a Markov model to extrapolate lifetime outcomes based on the data from this study combined with literature data. The EQ-5D-5 L, ICECAP-O, and CarerQol-7D data will be transformed into QALYs for patients and caregivers (well-being years for ICECAP-O), using published tariffs obtained from general reference populations [90, 91].

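### The 80% power stated for N = 86 is for one outcome at alpha 0.05 and a test that is not the planned comparison; N = 150 may stand, but its power should be restated

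*Protocol article*

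**What the plan says.** All references are to the protocol article.

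- **Sample size.** Two earlier studies are cited as the basis for the effect: "Both studies showed a moderate effect size for the effects of PCC interventions on QoL". Because validated methods for the mixed model are said to be limited, "our calculation is based on a repeated measures ANOVA". The result is N = 86 and N = 46 "for between- and within-group analyses, respectively, based on a power of 0.80 and an alpha of 0.05". The plan is to enrol 75 + 75 = 150, "which exceeds the estimated needed sample size, even when accounting for dropout/loss to follow-up". No numerical effect size, number of measurements, correlation or dropout rate is given.
- **Abstract and Study design.** Patient quality of life and caregiver quality of life are both primary.
- **Primary outcomes and Table 2.** Patient quality of life is the QoL-AD and caregiver quality of life is the CarerQol-7D. For the QoL-AD, "The proxy version of the QoL-AD is also used and filled out by the caregiver".
- **Statistical methods.** "We will correct for multiple testing". Linear mixed models over T0, T1 and T2 compare the groups' trajectories, with the baseline measure as a fixed effect.
- **Outcome measures.** T0 is a baseline measurement, before treatment.

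**The concern.** Three parts of the power statement do not match the analysis described one section later.

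1. **Alpha.** The full 0.05 is spent on one outcome, although there are at least two primary outcomes and a correction is promised. If the correction covers them, no primary test is assured of the 0.05 level.
2. **Contrast.** A repeated-measures between-group main effect is not a comparison of trajectories or a baseline-adjusted difference. If it is averaged over T0, T1 and T2, it also presumes a group difference before treatment.
3. **The second figure.** A within-group change cannot separate DICE from usual care, so N = 46 gives no support for the size of a comparative study.

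At stake is the margin that the reader is told exists, 150 against 86. How much of it remains depends on the contrast and the corrected alpha, and the section fixes neither.

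**Working it through.** **Inputs.** From the document: power 0.80, alpha 0.05, two equal groups, planned N = 150, three time points. Assumed, because not printed: a moderate effect taken as f = 0.25 (0.5 SD), m = 3 measurements, correlation rho = 0.5. Corrected alpha is shown as 0.05/2 = 0.025 (two primaries) and 0.05/3 = 0.0167 (three scores). Dropout is illustrated at 20%: 150 × 0.8 = 120 completers. All powers use the noncentral F distribution.

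**Step 1: reproduce 86.** Between-group main effect: λ = N·m·f²/(1 + (m − 1)·rho), with 1 and N − 2 degrees of freedom. At N = 86: λ = 86 × 3 × 0.0625/2 = 8.06, power 0.801. This is the smallest even N reaching 0.80, so 86 reproduces.

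**Step 2: same test, corrected alpha.**

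| Alpha | Power at 86 | N for 0.80 | Power at 150 | Power at 120 |
|---|---|---|---|---|
| 0.05 | 0.80 | 86 | 0.96 | 0.91 |
| 0.025 | 0.71 | 104 | 0.93 | 0.86 |
| 0.0167 | 0.65 | 116 | 0.91 | 0.82 |

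The planned 150 absorbs 1 − 104/150 = 31% loss at alpha 0.025, or 1 − 116/150 = 23% at 0.0167.

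**Step 3: try to reproduce 46.** Within-group effect: λ = N·m·f²·ε/(1 − rho), where ε is the sphericity factor. The Step 1 inputs give N = 28 with ε = 1, and 44 with ε = 0.5, the lowest value possible for m = 3. With m = 2 and rho = 0.31 to 0.33, both 86 and 46 are obtained. The inputs behind 86 therefore cannot be settled from the article.

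**Step 4: if 86 is the average over T0, T1 and T2.** With 0.5 SD at T1 and T2 and none at T0, the mean difference is 0.5 × 2/3, so f = 0.25 × 2/3 = 1/6. That test at alpha 0.05 would need 192, and 150 would give 0.70. This shows why the test is unsuitable. It is not the power of the trial, because the planned model is a different one.

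**Step 5: contrasts of the planned kind, effect 0.5 SD.**

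Baseline-adjusted difference at T2: λ = (N/4)·0.5²/(1 − rho²), with 1 and N − 3 degrees of freedom.

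| Alpha | N | rho 0.3 | rho 0.5 | rho 0.7 |
|---|---|---|---|---|
| 0.025 | 150 | 0.83 | 0.90 | 0.98 |
| 0.025 | 120 | 0.73 | 0.81 | 0.94 |
| 0.0167 | 150 | 0.78 | 0.87 | 0.97 |
| 0.0167 | 120 | 0.67 | 0.77 | 0.92 |

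Group-by-time test with differences 0, 0.5 and 0.5 SD: λ = (N/4)·SS/(1 − rho), where SS is the sum of squared deviations of the three differences from their mean (0.167), with 2 and 2(N − 2) degrees of freedom. At rho = 0.5, power at 150 is 0.83 (alpha 0.025) or 0.79 (0.0167); at 120 it is 0.72 or 0.67.

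**The case against.** The strongest reply is that the article presents repeated-measures ANOVA openly as a stand-in, that a journal article need not print every input, and that 150 is well above 86. Much of this stands.

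- A reader might infer that the trial is underpowered. The documents do not support that. On the plan's own type of test, 150 keeps 0.91 even at the strictest alpha considered, and 0.82 with 120 completers. The failing values in Step 4 require both the inferred inputs and a test that the Statistical methods section does not plan to use.
- A reader might take it as fact that the calculation counts baseline as treated. It is an inference. The inputs that give 86 with three measurements give 28, not 46, for the within-group figure, and a two-measurement set gives both printed figures. Two measurements could be T1 and T2, with no baseline in the between-group test.
- Three primary scores is the stricter reading. The proxy QoL-AD is not said to be tested separately, and the family covered by the correction is not defined. Leaving that detail to an analysis plan is ordinary.

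The reply does not remove the mismatch between a power statement at 0.05 for one outcome and a promised correction with at least two. Choosing ANOVA as a stand-in does not force the choice of a main effect either, since the group-by-time interaction is available in the same framework.

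**Conclusion.** The point holds in limited form. The 80% power attached to N = 86 does not describe the multiplicity-corrected, baseline-adjusted trajectory comparison that is planned. On the same test, and if the correction covers the primary outcomes, the requirement is 104 or 116 rather than 86. That size rests on f = 0.25, m = 3 and rho = 0.5, which are assumed, and on an equal split of alpha. N = 46 does not follow from those inputs and is irrelevant to the comparison with usual care.

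The adequacy of 150 is not refuted, but the printed calculation does not establish it. With 20% dropout and rho = 0.5, power runs from 0.67 (group-by-time, alpha 0.0167) to 0.81 (baseline-adjusted T2, alpha 0.025). The claim of sufficiency after dropout therefore depends on choices that the section does not state.

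**What to change.** Keep N = 150 and rewrite the power paragraph:

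- Name the between-group contrast to be powered: the baseline-adjusted difference at T2, or group-by-time.
- State the effect size as a number, a correlation range such as 0.3 to 0.7, the alpha after correction for the primary outcomes (saying whether the proxy QoL-AD counts separately), and an assumed dropout rate.
- Report the resulting power at 150 and at the expected number of completers, in place of the claim that 150 exceeds 86.
- Do not use the within-group figure of 46 to justify the size.

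The cost is one rewritten paragraph and a less favourable stated margin. Enrolment does not change.

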### Statistical methods

*T*-tests or chi-square tests will be used to identify the differences in baseline characteristics (e.g., age, education level, disease severity) between the control group and the intervention group. For the primary and secondary study outcomes, we will use an intention-to-treat approach including all subjects irrespective of the adherence to our intervention [89]. Thereafter, we will perform per-protocol analyses with only the subjects who completed the intervention (underwent all DICE steps). We will correct for multiple testing.

We will use the Little’s Missing Completely at Random Test to examine whether the data are missing at random or missing completely at random. The mixed model analyses will be able to handle the data when the missing data is completely at random. Multiple imputation will be used in cases when data is missing at random.

Linear mixed models will be used for the primary and secondary outcomes for the T0, T1, and T2 time points. These statistics are preferred when using longitudinal data because of its advantage in handling missing data and its capacity to deal with nested data and variance in follow-up duration between and within the groups. Changes in the trajectories of the primary and secondary outcomes are compared between the two groups. Subject, hospital, and time are considered as random effects, and baseline measure, group, and disease severity are accounted as fixed effects.

We will perform a cost-utility analysis of the intervention group versus the control group in accordance with the Dutch guidelines for economic evaluations on the basis of questionnaires [90].

Quality and length of life will be combined into quality-adjusted life years (QALYs) using a Markov model to extrapolate lifetime outcomes based on the data from this study combined with literature data. The EQ-5D-5 L, ICECAP-O, and CarerQol-7D data will be transformed into QALYs for patients and caregivers (well-being years for ICECAP-O), using published tariffs obtained from general reference populations [90, 91].

With the simple Markov model, we will calculate the incremental effectiveness of the DICE method versus the control group in QALYs, incremental costs, and the incremental cost-effectiveness ratios. We will also perform one-way, two-way, and probabilistic sensitivity analyses to determine the effect of uncertainty in all input parameters. Using a non-parametric bootstrapping (randomly drawing 5000 observations with replacement from the patient sample), the degree of uncertainty for costs and health effects and the cost-utility ratio will be depicted. In addition, an acceptability curve will be drawn, which indicates the probability that the intervention studied has lower incremental costs per QALY gained than various thresholds.

A budget impact analysis will be performed that includes relevant features and tariffs of the Dutch healthcare system; anticipated uptake of the new intervention as well as usual care will be considered. The budget impact per year of implementing the new intervention will be estimated. All elements of medical costs for the intervention group and the control group will be considered and calculated.

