### Outcome measures

For the control group, measurements will take place at baseline (T0), with follow-up testing at 3 months (T1) and 6 months (T2). For the intervention group, measurements will take place at baseline (T0), directly after treatment (T1), and follow-up at 6 months (T2). The T1 measurements will be planned after finishing the (psychosocial) intervention and/or when medication is stabilized and thus may vary between subjects in the intervention group. We will gather all relevant clinical and intervention-related information which enables us to study post hoc whether this variation in T1 assessments may have resulted in bias. All measurements will take place at the local hospitals or at the patients’ homes, see Table 2 for an overview of all outcome measures.

**Table 2 Tab2:** Outcome measures

Outcome	Measure	Purpose	Respondent	Time of assessment
Demographic characteristics	For example, age, education, sex, ethnicity, relation to caregiver	Descriptive, covariate, moderator	Patient and caregiver	T0
Clinical characteristics	For example, diagnosis, AD biomarkers, disease duration	Descriptive, moderator	Patient and caregiver	T0*
Disease severity	CDR [57]	Descriptive, moderator	Patient	T0*, T2
Cognitive status	MMSE [58]	Descriptive, moderator	Patient	T0*, T2
Cognitive functioning	Standardized cognitive test battery [43]: RAVLT [59], VAT [60], DS [61], VF [62], LDST [63], SCWT [64], TMT [65]	Descriptive, moderator	Patient	T0*
Functional abilities	A-IADL-Q [66]	Descriptive, moderator	Caregiver	T0, T2
Psychotropic medications	Brown bag review [20]	Descriptive, secondary outcome	Caregiver	T0, T1, T2
Comorbidities	CIRS-G [50]	Descriptive	Patient	T0, T2
Quality of life patient	QoL-AD [67]	Primary outcome	Patient and caregiver	T0, T1, T2
Quality of life caregiver	CarerQol-7D [53]	Primary outcome	Caregiver	T0, T1, T2
Caregiver burden	Perseverance time [68]	Secondary outcome	Caregiver	T0, T1, T2
Caregiver competence managing NPS	Additional NPI-Q item [69]	Secondary outcome	Caregiver	T0, T1, T2
Cost-effectiveness	EQ-5D-5 L [70], ICECAP-O [71] iMTA iVICQ [72], iMTA MCQ [73]	Secondary outcome	Patient Caregiver	T0, T1, T2
NPS prevalence, severity, and distress	NPI-Q [44]	Secondary outcome	Caregiver	T0*, T1, T2
If NPI-Q frequency score ≥ 1 on:				
“Agitation,” “motor disturbances,” “irritability,” “disinhibition”	Cohen-Mansfield Agitation Inventory [74]	Secondary outcome	Caregiver	T0, T1, T2

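### The listed mixed-model terms have no fixed time or group-by-time effect and use T0 as both response and covariate, so they cannot make the promised trajectory comparison

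*Protocol article*

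**What the plan says.** Three consecutive statements in the Statistical methods section of the protocol article describe the analysis of all primary and secondary outcomes.

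- Response: "Linear mixed models will be used for the primary and secondary outcomes for the T0, T1, and T2 time points".
- Aim: "Changes in the trajectories of the primary and secondary outcomes are compared between the two groups".
- Terms: "Subject, hospital, and time are considered as random effects, and baseline measure, group, and disease severity are accounted as fixed effects".

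The article does not say whether time enters as a random intercept or as a subject-level random slope. Under Outcome measures, T0 precedes treatment. T1 is at 3 months in controls, but in the intervention group it follows the end of treatment and "thus may vary between subjects in the intervention group". On missing data, the plan relies on the mixed model when values are missing completely at random and on multiple imputation when they are missing at random. The Study design section describes two sequential, non-randomised waves that are assumed to be similar at baseline.

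**The concern.** A between-group comparison of trajectories needs a parameter for it, normally a group-by-time term. The listed fixed effects are baseline, group and disease severity only. Time appears solely among the random effects. A random time effect is a variance component common to both groups; it is not a contrast between them. The one treatment term left is a group main effect pooled over T0, T1 and T2.

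T0 is also both modelled and conditioned on. Given T0, the groups cannot differ at T0, so that visit adds a zero to the pooled group effect. At stake are the reported effect sizes and confidence intervals for QoL-AD and CarerQol-7D, the two primary instruments, and for the secondary outcomes. Readers will judge clinical relevance from these figures.

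**Working it through.** **Inputs.** From the article: T0, T1 and T2 as responses; the listed random and fixed terms; 75 per group; alpha 0.05 and power 0.80. The effect size is given only as moderate ("Both studies showed a moderate effect size for the effects of PCC interventions on QoL"). Assumed, because the article gives no figure: true effect d = 0.50 SD at T1 and T2, zero at T0; within-person correlation ρ = 0.5; unit SD; time coded 0, 1, 2; no missing data. Hospital and disease severity were left out of the check.

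**The plan's own figure.** For the between-group repeated measures ANOVA, λ = f²·N·m / (1 + (m − 1)ρ). With assumed f = 0.25 (d = 0.5), m = 3 and ρ = 0.5, N = 86 gives λ = 0.0625 × 86 × 3 / 2 = 8.06 on 1 and 84 df, and power 0.801. This matches the stated N = 86, so d = 0.5 and ρ = 0.5 are reasonable values for illustration.

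**What the group coefficient estimates.** Each listed fixed covariate has the same value at all three visits of a subject. With complete data, the generalised least squares group coefficient is therefore the coefficient from regressing w₀T0 + w₁T1 + w₂T2 on T0 and group. The weights come from the fitted covariance matrix V: w = V⁻¹1 / (1′V⁻¹1). Given T0, the group effect at T0 is zero, so

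group coefficient = w₀·0 + w₁·d₁ + w₂·d₂.

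**Random intercepts.** All weights are 1/3, so the coefficient is (0 + 0.50 + 0.50)/3 = 0.333, two thirds of the effect. A random intercept for visit, shared by both groups, cancels and changes nothing. Scaled to 75 per group, a large simulated data set gave:

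| Model | Estimate | SE | Ratio |
|---|---|---|---|
| Listed terms | 0.331 | 0.0770 | 4.29 |
| T1 and T2 only, adjusted for T0 | 0.496 | 0.1156 | 4.29 |

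Estimate and SE shrink together, so the test is unchanged (power 0.994 for both in 500 simulated trials). The interval is not: in 1000 runs the listed model's 95% CI covered 0.50 in 41% of runs, against 96% for the T1/T2 model.

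**Subject-level random slope added.** The fitted weights become about 0.59, 0.33 and 0.08, so the coefficient is 0.33 × 0.50 + 0.08 × 0.50 = 0.205, or 0.41 of the effect. Simulated power falls from 0.994 to 0.864.

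**Range.** The scenarios used ρ of 0.5 or 0.7, unequal T1 and T2 effects, a common decline and true slope variance. The retained fraction was 0.66 to 0.68 with random intercepts (simulation noise around 2/3) and 0.31 to 0.51 with a random slope.

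**Source of the dilution.** With random intercepts, keeping T0 as both response and covariate but adding fixed visit and group-by-visit returns 0.50 at T1 and T2. The missing terms cause the loss.

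**Are the two standard repairs interchangeable?** Suppose the waves differ by δ at baseline and the difference persists. Adjusting T1/T2 for T0 estimates d + (1 − ρ)δ. Modelling T0, T1 and T2 with group-by-time estimates d. With ρ = 0.5 and assumed δ = +0.3 SD, the first gives 0.50 + 0.15 = 0.65; with δ = −0.3 SD it gives 0.50 − 0.15 = 0.35. The second gives 0.50 in both cases.

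**The case against.** The strongest reply is that a condensed article need not print a full model formula. The list of terms is not declared exhaustive, the article never names the group main effect as the reported estimate, and the sentence before the list commits to comparing trajectories. If the analysts add the interaction, the contrast is not diluted, even with T0 used twice.

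Much of this stands, and it rules out several inferences a reader might draw.

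- That trajectories will not be compared. The article says they will be; the listed terms simply do not do it.
- That the effect is diluted by exactly one third. That fraction needs random intercepts and complete data. Variable T1 timing, and the stated wish to handle differing follow-up durations, make a time slope at least as plausible, and the loss is then larger.
- That using T0 twice is itself the source of bias. It is not, once group-by-visit is present. It then leaves unclear whether a baseline-adjusted difference or a difference in change is meant.
- That dropout makes the dilution worse in general. With T1 and T2 values missing and no imputation, a simulation gave 0.31 SD. Where the planned multiple imputation is used, the data are complete again and the factor returns to two thirds.

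What does not stand is the appeal to omitted detail. The article states which effects are fixed and which are random, and it places time explicitly among the random effects. This is a specification that conflicts with the stated aim.

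**Conclusion.** The point holds in conditional form. The listed terms cannot make the trajectory comparison that the same paragraph promises. If the listed model's group coefficient is reported as the treatment effect, it understates the post-baseline effect. It retains two thirds with random intercepts and complete or imputed data, and about 0.3 to 0.5 with a subject-level random slope.

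The two-thirds factor on the mean T1/T2 effect is algebra and does not depend on effect size or correlation. The random-slope range and the power and coverage figures rest on assumed values that the article does not give. Under random intercepts the damage is to the estimate and interval, not to the test; under random slopes power also suffers. Because this affects the primary estimates and costs only wording, it should be corrected before analysis.

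**What to change.** Restate the primary model with time as a fixed effect and a group-by-time term, and name that contrast as the treatment effect. Use T0 in one role only:

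- (a) T1 and T2 as responses, with the T0 value as covariate; or
- (b) T0, T1 and T2 as responses, without the baseline covariate.

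In a non-randomised, sequential design these can answer differently if the waves differ at baseline. Prespecify one as primary, give the reason, and report the other as a sensitivity analysis. State also whether any random time effect is an intercept or a subject-level slope. Making T2 the primary contrast, or hospital a fixed effect, is optional and not needed for the repair.

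The cost is a change of wording in the analysis plan. No new data or visits are required.
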